### Recruitment {15}

Foetuses with CDH are usually identified via antenatal screening and clinical NICU teams alerted prior to their delivery. Infants with CDH, who may be suitable for the clinical trial, will be identified following a daily discussion with the NICU team. Following delivery, infants will be screened for their eligibility to participate within the trial. As part of the routine standard of care, CDH infants will receive an echocardiogram within the first few days of life, enabling the identification of any associated cardiac anomalies.

On average, each NICU admits one CDH neonate per month. We aspire to recruit eighteen infants between August 2023 and August 2024.

### Consent or assent {26a and 26b}

Parents/legal guardians of infants with CDH that meet eligibility criteria will be informed of the trial by a named clinical consultant. At this stage, the clinical team will provide consenting adults with a participant information sheet (PIS). If interested in participating, a member of the research team will organise a face-to-face interview with parents/legal guardians. This meeting will provide parents an opportunity to ask any further questions regarding the study. It will be emphasised in this meeting that choosing not to participate will not affect their infant’s care. Informed written consent will be obtained.

No biological specimens will be collected or stored for study purposes. Blood tests to monitor the effect of ventilatory settings will be performed as part of routine clinical care.

### Allocation and blinding {16a, 16b, 16c, 17a and 17b}

Each infant in this study will be randomised to receive NAVA or ACV in a 1:1 ratio using computer generation sequence methodology.

The clinical team and study investigators will know which study intervention is assigned to each patient. The independent statistician will be blinded to each study arm.

### Provisions for post-trial care {30}

Post-trial care is the responsibility of treating clinicians. Patients will not receive financial compensation for their participation in the study.

### Participant timeline {13}

Screening of participants begins once they have received 24 h of invasive ventilation. Eligible patients will be enrolled into a VSTT. If participants pass the VSTT, they will be randomised to receive either NAVA or ACV first. Participants remain on the assigned ventilator mode for 4 h. Primary outcomes will be recorded for the final 30 min of each ventilation period. Infants will undergo a 20-min stabilisation period prior to receiving the second mode of ventilation for 4 h. There are no follow-up visits of data collection following the total ventilation period (Fig. 1).

**Fig. 1 Fig1:**
[figure not shown]
Participant timeline from screening to discharge from the NAN-C trial

### Research ethics and approval {24}

Favourable ethical opinion was granted by the West of Scotland REC. Written, informed consent to participate will be obtained from all parents/legal guardians of eligible children.

### Plans for communicating important protocol amendments to relevant parties (e.g. trial participants, ethical committees) {25}

The co-ordinating committee is responsible for the distribution of protocol amendments to site investigators. Site investigators are responsible for the distribution of amendments to all staff involved within the study and for obtaining approval from the local research ethics committee as required.

### Authorship {31b}

Investigators will be invited to contribute to writing and reviewing the primary manuscripts and abstracts.

### Frequency and procedures for auditing trial conduct {23}

On-site and virtual monitoring activities will be used to ensure the quality of data captured, study operations and patient safety. A risk-based approach will govern the monitoring activities of each NICU. The site investigator will permit study-related monitoring, audits, and inspections by the REC, the sponsor, of all study-related documents. The site investigator will ensure the capability for inspections of applicable study-related facilities.

## Interventions

### Intervention description {11a}

A six-French (6 FR) specialised nasogastric tube (EAdi Catheter) is inserted to monitor electromyogram of the crural diaphragm. Correct position of the EAdi catheter is confirmed as per instructions of the manufacturer (Maquet, Servo-n user manual version 4.1) [13]. The guide function displays the retrocardiac echocardiograph. Correct positioning is when the P waves and QRS complexes are visible in the upmost leads and then decrease in size until the P waves disappear in the lowest leads. Coloured highlighting of the central two leads will also appear once the catheter is in the correct place. Once correct positioning is confirmed, the catheter will be securely attached to the infant’s face using an adhesive dressing.

Before infants are changed to NAVA mode (*Servo-n ventilator, Maquet Critical Care, Solna, Sweden*), the NAVA level will be adjusted by the clinician, so the display pressure waveform closely matches the actual pressure waveform, aiming for peak Edi between 5 and 15 microvolts (μV).

On recruitment into the trial, infants will undergo a 1-h VSTT. At King’s College Hospital NHS Foundation Trust infants will be transferred from the SLE 6000 Ventilator (Software versions 4.3; SLE Ltd; South Croydon, UK) to the servo-n ventilator (Maquet Critical Care, Solna, Sweden) for the VSTT. At St. George’s University Hospital NHS Foundation Trust, infants will remain on ACV using the servo-n ventilator (Maquet Critical Care, Solna, Sweden). At this stage, infants requiring an FIO2 of more than 80% to maintain SpO2 85–95%, or requiring nitric oxide infusion, will be excluded.

Infants will then be randomised to receive either ACV or NAVA ventilation modes on the servo-n ventilator for the first 4-h period. All infants will then undergo a 20-min stabilisation period. Following the stabilisation period, infants will then cross-over to receive the alternative ventilatory mode on the servo-n ventilator (Fig. 2)*.*

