### Eligibility criteria {10}

We will include neonates (< 28 days of life) with CDH. Eligible Infants will be identified daily by a researcher following discussion with the clinical team. The full inclusion and exclusion criteria can be found outlined in Table 1. Parents of participants meeting all the screening inclusion criteria and none of the screening exclusion criteria will be approached to give consent for their infant’s participation. Post-operatively, infants will then be enrolled within the study and proceed to a ventilatory support tolerance trial (VSTT).

**Table 1 Tab1:** Inclusion and exclusion criteria for participation {10}

Inclusion criteria	Exclusion criteria
▪ Infants born with a congenital diaphragmatic hernia at a gestation age of more than 34 weeks	▪ Known chromosomal anomaly
	▪ Cardiac anomalies expected to require corrective surgery in the first 60 days of birth
	▪ Renal anomalies associated with oligohydramnios
	▪ Skeletal deformities impeding lung or thoracic development
	▪ Severe anomalies of the central nervous system. Including neurological trauma or raised intracranial pressure
	▪ Neuromuscular blocking agent use
	▪ Contraindication to nasogastric tube insertion
	▪ Nitric oxide requirement
	▪ FiO_2_ greater than 80% at the end of the ventilatory support tolerance trial

For the VSTT, neonates will be stabilised for an hour on ACV on the servo-n ventilator (Maquet Critical Care, Solna, Sweden). The positive end-expiratory pressure (PEEP) will be kept 4–5cm H_2_O and inflation time at 0.36–0.4 s. The fraction of inspired oxygen concentration (FiO_2_) will be adjusted with the aim of maintaining oxygen saturations between 85 and 95%. At this stage, infants requiring an FiO_2_ greater than 80% to maintain their oxygen saturation, or requiring nitric oxide, will be excluded.

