### Outcomes {12}

The primary outcome of the study is the average OI for the final 30 min of each 4-h ventilatory period. OI is calculated as MAP x FiO_2_ × 100/PaO_2_ [14]. The OI is often used as an indicator of hypoxemic respiratory failure (HRF) and in infants with CDH is the leading criterion to administer inhaled nitric oxide (iNO) or initiate extracorporeal membrane oxygenation therapy (ECMO) [15, 16]. Previous research has demonstrated a 1-h period is sufficient to compare OI between NAVA and ACV [17]. We have decided on a 4-h period to allow neonates sufficient time to stabilise on the ventilatory mode.

The secondary outcome measures and monitored variables will include:(i)The average respiratory severity score (RSS) during the final 30 min of each 4-h ventilation period. The RSS is calculated as FIO_2_ x MAP. It will be calculated prior to randomisation, post randomisation and following cross-over.(ii)Average MAP during the final 30 min of each 4-h ventilation period.(iii)Initial ventilator settings and the number of de-saturations, defined as an SpO2 of less than 88%, will be noted for each neonate.(iv)Average PIP during the final 30 min of each 4-h ventilation period.(v)Cumulative total concentration of morphine-equivalent use will be recorded 4-h prior to ventilation with ACV or NAVA. In addition, total morphine-equivalent use during each 4-h ventilation period will be recorded and compared.(vi)Cumulative total concentration of midazolam use will be recorded 4-h prior to ventilation with ACV or NAVA. In addition, midazolam use during each 4-h ventilation period will be recorded and compared.

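### NAVA's 4-h window opens at a mode change in more infants than ACV's, so the whole-period morphine-equivalent and midazolam comparisons can be biased by the switch itself

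*Protocol article*

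**What the plan says.** - **Run-in.** Eligibility criteria {10}: "For the VSTT, neonates will be stabilised for an hour on ACV on the servo-n ventilator". This applies at both sites and before either sequence.
- **Period 1.** Intervention description {11a}: "Infants will then be randomised to receive either ACV or NAVA ventilation modes on the servo-n ventilator for the first 4-h period". No further interval is described between the tolerance trial and this period.
- **Period 2.** Participant timeline {13}: "Infants will undergo a 20-min stabilisation period prior to receiving the second mode of ventilation for 4 h". Intervention description {11a} places the switch after that interval: "All infants will then undergo a 20-min stabilisation period. Following the stabilisation period, infants will then cross-over to receive the alternative ventilatory mode". The text does not say which mode runs during the 20 min.
- **Allocation.** Allocation and blinding: "Each infant in this study will be randomised to receive NAVA or ACV in a 1:1 ratio", that is, 9 infants per sequence expected among 18.
- **Outcome windows.** Outcomes {12} explains the period length: "We have decided on a 4-h period to allow neonates sufficient time to stabilise on the ventilatory mode". OI, RSS, MAP and PIP are averaged over the last 30 min. For opioids, "total morphine-equivalent use during each 4-h ventilation period will be recorded and compared", and midazolam is treated the same way. Desaturations are to be noted per infant, with no window and no comparison between modes stated.
- **Importance.** Objectives {7} names sedative use as the one specific secondary outcome.

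**The concern.** An infant allocated ACV first begins the ACV window after an hour already on that mode. An infant allocated NAVA first begins the NAVA window at the change. The run-in is the same for everyone, so the reverse sequence does not mirror this.

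The protocol accepts that infants need time to settle and shields the respiratory outcomes by reading them late in each period. The sedative totals have no such shield. If a mode change alters dosing for a while, the change is counted under NAVA more often than under ACV, even when the settled modes are identical. What is at stake is the interpretation of the sedation comparison.

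**Working it through.** **Inputs.** From the protocol: 18 infants, 1:1 sequence allocation, 240-min windows, a 60-min ACV run-in and a 20-min interval before period 2. The protocol gives no figure for this point. Its 18 is used only as a denominator; it is reproduced by a two-sided 5% paired t-test for a 1-SD difference with uncorrelated periods (power 0.807).

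**Step 1: which windows open at a mode change (9/9 split).**

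| 20 min spent on | NAVA-first: NAVA / ACV window | ACV-first: ACV / NAVA window | NAVA total | ACV total |
|---|---|---|---|---|
| (a) outgoing mode (literal reading) | yes / yes | no / yes | 18 | 9 |
| (b) incoming mode | yes / no | no / no | 9 | 0 |
| (c) ACV for all | yes / no | no / yes | 18 | 0 |

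The gap is 9/18 = 50 percentage points under (a) and (b), and 18/18 = 100 under (c). Under simple randomisation the 95% range for the number allocated NAVA first is 5 to 13. The gap is then 5/18 to 13/18 (28 to 72 points) under (a) and (b), and stays at 100 under (c).

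**Step 2: randomised order does not cancel it.** Let d be the effect of a switch on a window total, with no true mode effect. The expected NAVA minus ACV difference is:
- (a) 0 in NAVA-first and d in ACV-first infants; mean 0.5d.
- (b) d in NAVA-first and 0 in ACV-first infants; mean 0.5d.
- (c) d in both; mean 1.0d.

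A period-adjusted estimate averages the two sequence means, so it carries the same bias.

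**Step 3: size under an assumed rate.** Assume dosing runs at k = 3 times the settled rate for T min after any switch. A window holding t min of transient then counts 240 + (k − 1)t settled-minute equivalents. Under (b), and for the switch to ACV under (c), the first 20 min of the transient fall in the interval, so t = T − 20.

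T = 20 (full transient 280, none 240):
- (a) NAVA 280; ACV (240 + 280)/2 = 260; 280/260 = 7.7% excess.
- (b) NAVA (280 + 240)/2 = 260; ACV 240; 8.3%.
- (c) NAVA 280; ACV 240; 16.7%.

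T = 60 (full transient 360, 40 min of spill-over 320, none 240):
- (a) NAVA 360; ACV (240 + 360)/2 = 300; 20.0%.
- (b) NAVA (360 + 320)/2 = 340; ACV (240 + 320)/2 = 280; 21.4%.
- (c) NAVA 360; ACV (240 + 320)/2 = 280; 28.6%.

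With k = 1 every excess is zero.

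**Step 4: false-positive rate.** Simulation with 18 infants (9/9), normal differences, no true mode effect, nominal two-sided 5%, 50,000 runs, d in SDs of the within-infant difference:

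| d | Paired t, (a) or (b) | Period-adjusted, (a) or (b) | Paired t, (c) |
|---|---|---|---|
| 0 | 5% | 5% | 5% |
| 0.25 | 8% | 8% | 17% |
| 0.5 | 16% | 17% | 52% |
| 1.0 | 42% | 52% | 98% |

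The values of d are assumptions, and the simulation treats the 20 min as absorbing any switch that occurs at its start.

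**The case against.** **No switch effect is documented.** The threefold rate and the 20- and 60-min transients are assumptions. The NAVA level is also adjusted before the change so that the pressure waveforms match, which may soften the transition. This stands: the text shows potential bias, not bias of known size.

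**Period 1 does have a stabilisation before it.** True, but it is on ACV only, and that is the source of the imbalance.

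**A 4-h total is a legitimate quantity.** Sedation needed to start a mode can be seen as part of that mode's cost. This stands, and is a reason to keep the totals. Even for that question the comparison is uneven, because ACV's starting cost is fully counted in at most half of the infants.

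**Dropping the first hour can mislead too.** A dose given at the switch may reduce later need, so a settled window would drop the dose and keep its benefit. This stands, and rules out replacing the totals.

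**Dose timing is not promised to the minute.** Relevant concomitant care {11d} speaks of daily doses and Data collection methods {18a} of patient notes. This stands in part. The 4-h totals already require doses to be placed in time within the day, so a cut at 60 min needs the same kind of record.

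**The mode during the 20 min may be settled elsewhere.** The figures and full protocol are not shown, so its absence from the text is not raised as a fault. The imbalance appears under all three readings.

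**A bias against NAVA could not create a false superiority claim.** True if switches raise dosing; it could still hide a benefit. If switches lower dosing, the bias runs the other way.

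**Conclusion.** The imbalance in how the windows open is real under every reading: 18 against 9 on the literal one, otherwise 9 against 0 or 18 against 0. It can bias the morphine-equivalent and midazolam comparisons by 0.5d to 1.0d, where d is an unknown switch effect that may be zero. Under the assumed threefold rate this is about 8% to 17% for a 20-min transient and 20% to 29% for 60 min.

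Four stronger readings are not supported:
- That the totals are skewed against NAVA. This needs switches to provoke dosing, which the documents do not show.
- That the 60-min excess reaches 50% (360/240) when the 20 min is on ACV. That ignores the 40 min of transient spilling into the ACV window of NAVA-first infants; 360/280 gives 29%.
- That desaturations are biased in the same way. This holds only if they are counted over the whole period and compared by mode, which Outcomes {12} does not say.
- That the primary outcome is at risk. OI, like RSS, MAP and PIP, is read from 3.5 h onward.

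**What to change.** Keep the 4-h morphine-equivalent and midazolam totals. Pre-specify beside them a comparison over the same settled minutes since the start of each mode, for example 60 to 240, which matches the hour the protocol already uses for its run-in. Report first-hour use separately by mode. If desaturations are to be compared between modes, state their window and split them in the same way.

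This changes outcome and analysis wording only, provided dose times are recorded finely enough to cut at 60 min. The costs are smaller counts in the settled window and the possibility that first-hour doses lower later need, so the settled comparison should be read together with the 4-h total, not in place of it.

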**Fig. 2 Fig2:**
[figure not shown]
Ventilation protocol for the NAN-C trial. At King’s College Hospital NHS Foundation Trust (KCH), infants are routinely ventilated using assist control ventilation on the SLE 6000 ventilator. If infants meet the eligibility criteria, they will be transferred from ACV on the SLE 6000 to ACV on the servo-n ventilator (in the above diagram, ventilation machine changes depicted by arrows). Infants will be stabilised on the servo-n ventilator for 1 h in the ventilatory support tolerance trial. If suitable, infants will then be randomised to receive either ACV or neutrally adjusted ventilator assist (NAVA) for 4 h. Following a 20-min stabilisation period, they will then receive the second mode of ventilation. At St. George’s University Hospital (SGH), infants are routinely ventilated on ACV on the servo-n ventilator. Following the VSTT, they will be randomised to either NAVA or ACV on the servo-n ventilator

### Criteria for discontinuing or modifying allocated interventions {11b}

The back-up mode set is pressure control ventilation (PCV). The FiO_2_ will be adjusted with the aim of maintaining oxygen saturations between 85 and 95, as per recommendations of the CDH Euro Consortium [4]. The trial will be ceased in any infant with an increase in fraction of inspired oxygen concentration more than 30%. Any infant failing to trigger the ventilator will be excluded. In all cases, reasons for exclusion will be thoroughly documented.

### Strategies to improve adherence to interventions {11c}

To improve adherence to study interventions, a researcher will remain by the bedside for the study period recording any changes made by the clinician responsible for adjustment of the ventilator, including any deviations from protocol.

### Relevant concomitant care permitted or prohibited during the trial {11d}

All non-respiratory NICU care will be at the discretion of the responsible clinical consultant and in line with the NICU’s guidelines. Guidelines for the administration of sedative medication and analgesia are provided by NICU, with a recommendation to use the lowest possible dose of sedative medication as required. We will record the daily dose of analgesia, sedative, and neuroleptic medications. All infants will be reviewed by a dietician to ensure the infant is receiving adequate calories, protein, and nutrients to meet their energy requirements.

### Explanation for choice of comparators {6b}

NAVA is a unique, closed-loop mode of mechanical ventilation that has been shown to optimise patient-ventilatory synchrony by responding directly to neonatal diaphragmatic signalling [9]. The aim of this study is to determine if NAVA is superior to ACV in achieving clinically important outcomes. ACV was chosen as the comparator as it is the standard of care for ventilating infants in many NICUs.

### Outcomes {12}

The primary outcome of the study is the average OI for the final 30 min of each 4-h ventilatory period. OI is calculated as MAP x FiO_2_ × 100/PaO_2_ [14]. The OI is often used as an indicator of hypoxemic respiratory failure (HRF) and in infants with CDH is the leading criterion to administer inhaled nitric oxide (iNO) or initiate extracorporeal membrane oxygenation therapy (ECMO) [15, 16]. Previous research has demonstrated a 1-h period is sufficient to compare OI between NAVA and ACV [17]. We have decided on a 4-h period to allow neonates sufficient time to stabilise on the ventilatory mode.

The secondary outcome measures and monitored variables will include:(i)The average respiratory severity score (RSS) during the final 30 min of each 4-h ventilation period. The RSS is calculated as FIO_2_ x MAP. It will be calculated prior to randomisation, post randomisation and following cross-over.(ii)Average MAP during the final 30 min of each 4-h ventilation period.(iii)Initial ventilator settings and the number of de-saturations, defined as an SpO2 of less than 88%, will be noted for each neonate.(iv)Average PIP during the final 30 min of each 4-h ventilation period.(v)Cumulative total concentration of morphine-equivalent use will be recorded 4-h prior to ventilation with ACV or NAVA. In addition, total morphine-equivalent use during each 4-h ventilation period will be recorded and compared.(vi)Cumulative total concentration of midazolam use will be recorded 4-h prior to ventilation with ACV or NAVA. In addition, midazolam use during each 4-h ventilation period will be recorded and compared.

### Dissemination policy {31a and 31c}

We plan to submit a manuscript for publication in an international journal and submit an abstract for presentation at an international meeting. For 6 months following the publication of the final study results, investigators will be granted priority for secondary data analyses. Following this period, requests for de-identified data will be considered. Requests for data presented in the final paper should be submitted via email to [name].

## Data collection and management

### Data collection methods {18a}

As per standard of care, outcome, baseline, and clinical care data are recorded by the clinical NICU team in the patient’s notes, which will serve as documents for trial data. Additional information related to trial outcomes will be recorded by authorised and trained members of the research team.

### Plans to promote participant retention and complete follow-up {18b}

As infants are receiving invasive MV for the duration of the trial, we expect complete follow-up in 95% of randomised patients. We anticipate a 5% loss-to-follow-up rate comprised of infants transferred to other hospitals, consent is withdrawn or become too unwell to participate in the trial.

